### Study population and recruitment

Based on other similar studies and the previously mentioned preschool study conducted by our research group [27], approximately 30% total non-participation is expected. Specifically, we expect an estimated accelerometer non-compliance rate of 10% (i.e., participants with insufficient wear time) and a dropout rate of 20% throughout the study period. Consequently, we aim to recruit approximately 4000 children aged 3–5 years from 100 public preschools within all 13 districts in the Stockholm region.

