**Methods:**

This proposed study is a pragmatic cluster-randomized controlled trial with two conditions (intervention and control with a 1:1 ratio) with preschools as clusters and the unit of randomization. We aim to recruit approximately 4000 3–5-year-old children from 90 preschools and retain more than 2800 children from 85 preschools to provide adequate statistical power for the analyses. The intervention to implement is a co-created, multicomponent policy package running for 6 months in preschools randomized to intervention. Change in accelerometer measured PA levels in children between intervention and control from pre- and post-intervention will be the primary outcome of the study, while secondary outcomes include health outcomes such as musculoskeletal fitness, psychosocial functioning, and absence due to illness in children among others. Implementation will be studied carefully using both quantitative (dose, fidelity) and qualitative (interview) methodologies. The change in primary and secondary outcomes, from pre- to post-intervention, will be analyzed with linear mixed-effect models (to allow both fixed and random effects) nested on a preschool level.

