### Sample size

The required sample size to obtain a statistical power of 0.90 was projected with a change in MVPA as the main outcome variable and by using the means and standard deviations of the aforementioned observational preschool study assessing PA [27]. A 5-min change in MVPA has been suggested in previous meta-analysis to be a reasonable target of clinical importance [35]. Assuming an effect size of 5 min MVPA, an intra-preschool correlation of 0.2, a standard deviation of 25, coefficient of variation of 0.3 (average preschool size of 35 children 3–5 years), and approximately 2800 children (from 85 preschools) should be retained.

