### Inclusion/exclusion criteria

Figure 1 illustrates the recruitment of preschools and subsequent recruitment of preschool children and teachers based on the inclusion/exclusion criteria. Due to the logistical burden and time limit of the study, only preschools with more than 60 enlisted children are eligible for participation. Despite restricting the invitations to preschools with more than 60 children enlisted, we expect that approximately 35 children per school will elect to participate. Children in the participating schools might, for example, elect not to participate due to COVID-19 or time constraints—limiting the number of children per school (cluster size). In order to ensure a representative sample in each district, approximately 30% of all public schools with more than 60 enlisted children (all age groups) in each district will be randomly asked to participate in the study. The random selection of preschools for study invitation will be fulfilled by contacting preschool principals following a random order of invitation generated by Stata (Additional file 2. programming codes, random_invatation_preschool) until the number of preschools agreed to participate reached approximately 30% of all public preschools in that district. The recruitment of preschool children and teachers will be initiated provided that preschool principals agree to participate. All 3–5-year-old children enlisted at the participating preschools will be invited to participate and the participation will be confirmed by the informed consent of parents. In addition, full-time teachers at the participating preschools will also be invited to participate and provide informed consent. Preschools with less than 10 children with parental informed consent and children who are not able to able to take part in PA measures (e.g., mobility disability) will be excluded from participation. The limit of at least 10 children with parental informed consent per preschool was chosen due to logistical reasons to accommodate the accelerometer measurement burden in the study.

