**Fig. 1 Fig1:**
[figure not shown]
Flowchart of study recruitment, randomization, and follow-up

A total of 156 preschools were asked to participate in the study and 127 preschools (with median of 11 preschools per district) with 3775 children and 448 teachers agreed to participate. Apart from 3 preschools that collected less than 3 parental informed consents, 124 preschools participated in the baseline data collection. No preschools were lost to follow-up.

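### The recruitment figures do not agree: 90 or 100 preschools, with 35 children per preschool used both before and after the 30% loss

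*Protocol article*

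**What the plan says.** All references are to the protocol article.

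- **Abstract, Methods:** the trial will recruit about 4000 "children from 90 preschools and retain more than 2800 children from 85 preschools".
- **Study population and recruitment:** "we aim to recruit approximately 4000 children aged 3–5 years" "from 100 public preschools within all 13 districts in the Stockholm region". The expected total loss is about 30%, made up of 10% accelerometer non-compliance and 20% dropout.
- **Sample size:** power 0.90, a 5-minute difference in MVPA, SD 25, intra-preschool correlation 0.2 and coefficient of variation 0.3, with an "average preschool size of 35 children". The stated result is about 2800 children from 85 preschools to be retained.
- **Inclusion/exclusion criteria:** "we expect that approximately 35 children per school will elect to participate". The same section bars from participation "Preschools with less than 10 children with parental informed consent".
- **Legend of Fig. 1:** 127 preschools with 3775 children agreed to take part. "Apart from 3 preschools that collected less than 3 parental informed consents, 124 preschools participated in the baseline data collection". No preschool was lost to follow-up.
- **Trial status:** recruitment is complete.

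**The concern.** Preschools are the unit of randomisation, so the number of preschools and the number of analysed children in each are the two central quantities of the sample size. The article gives two values for the number to recruit.

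It also uses 35 per preschool in two ways. In the sample size section it stands beside the total to be retained, so it describes the analysed cluster. In the inclusion criteria it is the number expected to join, from which the 30% has still to be lost. If 35 enrol, about 24.5 remain. If about 33 are to remain, roughly 47 must enrol (32.9/0.70 = 47.0), unless whole preschools also drop out.

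At stake is whether a reader can tell which design the stated power refers to. With these figures that is not possible.

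**Working it through.** **Reproducing the stated headcount.** Required enrolment = retained / (1 − loss) = 2800 / 0.70 = 4000. If the two losses multiply, retention is 0.90 × 0.80 = 0.72 and enrolment is 2800 / 0.72 = 3889. The target of about 4000 therefore follows from 2800 and the stated loss.

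**Children per preschool implied by 4000.** 4000 / 90 = 44.4 and 4000 / 100 = 40.0. Neither is 35.

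**Yield at 35 enrolled per preschool.**

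| Preschools | Enrolled | Retained at 0.70 | Retained at 0.72 | Shortfall from 2800 |
|---|---|---|---|---|
| 90 | 3150 | 2205 | 2268 | 19–21% |
| 100 | 3500 | 2450 | 2520 | 10–13% |

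Preschools needed at 35 enrolled: 4000 / 35 = 114.3, or 3889 / 35 = 111.1 with multiplicative losses.

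**Analysed cluster size.** The stated totals give 2800 / 85 = 32.9, and 85 × 35 = 2975. After a 30% loss from 35 the size is 35 × 0.70 = 24.5, and 85 × 24.5 = 2083.

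**Effect on power.** Inputs from the sample size section: difference 5, SD 25, ICC 0.2, CV 0.3. Alpha is not stated there; two-sided 0.05 is assumed.

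- Design effect: DE = 1 + ((CV² + 1)m − 1) × ICC, where m is the mean cluster size.
- Effective number per arm: n = (K × m / 2) / DE, where K is the total number of preschools.
- Power = Φ(5 / (25√(2/n)) − 1.96).

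| Design (K × m) | DE | n per arm | Power |
|---|---|---|---|
| 85 × 32.9 (as stated) | 7.98 | 175 | 0.47 |
| 90 × 24.5 | 6.14 | 180 | 0.47 |
| 100 × 24.5 | 6.14 | 199 | 0.52 |
| 124 × 21.3 (achieved) | 5.44 | 243 | 0.60 |

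The last row uses 3775 × 0.70 = 2643 expected analysable children, and 2643 / 124 = 21.3 per preschool. Without the CV term, the stated design reaches 0.50 instead of 0.47.

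As a sensitivity check only, an ICC of 0.05 (an assumption; the protocol says 0.2) gives 0.89, 0.87, 0.91 and 0.94 in the same order. Under either ICC, the difference between 85 × 32.9 and 90 × 24.5 is below two percentage points.

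**The case against.** The strongest reply is that this is a reporting slip without consequence. Much of that stands. Both places state the target as about 4000 children, and 4000 less 30% is 2800. A reader might infer that the recruitment target fails to deliver the retained sample. It does not: the shortfall appears only when the preschool count is multiplied by 35.

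A reader might also infer that the smaller clusters cost power. The table shows otherwise: at the protocol's ICC, each alternative has at least as much power as the stated design, because additional preschools outweigh fewer children in each. Recruitment then exceeded both preschool targets, with 124 at baseline.

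A second reply is that some of the 30% may come from whole preschools leaving (90 or 100 down to 85), so that the remaining preschools keep more than 24.5 each. The total retained does not change. Spread over 85 preschools it gives 2205 / 85 = 25.9 to 2520 / 85 = 29.6, still below 32.9.

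A third inference concerns the consent rule. The stated limit is 10 consents, while the only preschools reported as not continuing had fewer than 3. One might suspect that randomised preschools will later be removed. The text does not support this: the rule bars preschools from participation, consent is collected before baseline, and randomisation follows baseline. There may also have been no preschool with 3 to 9 consents, and the flowchart itself is not shown.

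None of these replies reconciles 90 with 100, or the two uses of 35.

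**Conclusion.** The inconsistency is real. The number of preschools to recruit is given as both 90 and 100, and 35 children per preschool cannot be both the enrolled and the analysed cluster size under a 30% loss. At 35 enrolled, either preschool count retains 10% to 21% fewer children than 2800. This rests only on the article's own figures, with losses taken as additive (0.70) or multiplicative (0.72).

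The consequence for power is small and does not run against the trial. The documents do not support a claim of under-recruitment in preschools, of a 4000 target that misses 2800, or of harm from the consent threshold. The gap between about 0.47 and the stated 0.90 arises from an ICC of 0.2 with 85 preschools. It is a separate matter and is not caused by the discrepancies described here.

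Correction is still warranted, because these are the figures on which the stated power rests and they describe a design that was not the one recruited. For the achieved design, power is about 0.60 at the protocol's own ICC, SD, difference and CV. That assumes two-sided alpha 0.05, the planned 30% loss and the design effect shown, with no gain credited for baseline adjustment.

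**What to change.** 1. State one preschool recruitment target in the abstract and in the recruitment section.
2. Say whether 35 is the enrolled or the analysed number per preschool, and make preschools, cluster size and retained total agree. Replacing 35 by 24.5 alone is not enough: 85 × 24.5 = 2083, so either 85 or 2800 must change as well.
3. As recruitment is complete, add the achieved figures: 124 preschools, about 3775 children, about 2640 expected to be analysable, about 21 per preschool. Give the power for that design with alpha and ICC stated. If an ICC other than 0.2 is used, give its source.
4. Add one sentence reconciling the 10-consent rule with the report of preschools with fewer than 3 consents, for example by saying whether any preschool had 3 to 9.

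The cost is a text correction and one rerun of the power calculation. No recruitment, data collection or trial conduct changes.

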### Inclusion/exclusion criteria

Figure 1 illustrates the recruitment of preschools and subsequent recruitment of preschool children and teachers based on the inclusion/exclusion criteria. Due to the logistical burden and time limit of the study, only preschools with more than 60 enlisted children are eligible for participation. Despite restricting the invitations to preschools with more than 60 children enlisted, we expect that approximately 35 children per school will elect to participate. Children in the participating schools might, for example, elect not to participate due to COVID-19 or time constraints—limiting the number of children per school (cluster size). In order to ensure a representative sample in each district, approximately 30% of all public schools with more than 60 enlisted children (all age groups) in each district will be randomly asked to participate in the study. The random selection of preschools for study invitation will be fulfilled by contacting preschool principals following a random order of invitation generated by Stata (Additional file 2. programming codes, random_invatation_preschool) until the number of preschools agreed to participate reached approximately 30% of all public preschools in that district. The recruitment of preschool children and teachers will be initiated provided that preschool principals agree to participate. All 3–5-year-old children enlisted at the participating preschools will be invited to participate and the participation will be confirmed by the informed consent of parents. In addition, full-time teachers at the participating preschools will also be invited to participate and provide informed consent. Preschools with less than 10 children with parental informed consent and children who are not able to able to take part in PA measures (e.g., mobility disability) will be excluded from participation. The limit of at least 10 children with parental informed consent per preschool was chosen due to logistical reasons to accommodate the accelerometer measurement burden in the study.

**Fig. 1 Fig1:**
[figure not shown]
Flowchart of study recruitment, randomization, and follow-up

A total of 156 preschools were asked to participate in the study and 127 preschools (with median of 11 preschools per district) with 3775 children and 448 teachers agreed to participate. Apart from 3 preschools that collected less than 3 parental informed consents, 124 preschools participated in the baseline data collection. No preschools were lost to follow-up.

### Randomization and blinding

Preschools will be stratified by the 13 Region Stockholm districts because geographical, organizational, and resource factors in each district are likely to differ and influence the implementation and effectiveness of the policy. After baseline assessment, preschools will be randomly assigned to the intervention or control condition by 1:1 ratio within each of the 13 districts to ensure equal representation of intervention and control preschools. Block randomization with districts as blocks is conducted with randomizr package in R (Version3.6.1) (Additional file 3. programming codes: randomization_preschool). A single-blinded approach will be adopted with outcome assessor and data analyst blinded to the treatment allocation. Since the intervention is open-label, with only the outcome assessors and data analysts blinded, emergency unblinding for participants will not occur.

### Intervention description

The intervention components were developed based on the aforementioned observational preschool study [27] and systematic review data on the effectiveness of PA interventions for preschoolers, i.e., (i) organizational changes at the policy level, (ii) unstructured outdoor play, and (iii) instructions to preschool personnel on how to encourage child PA behaviors [21]. The intervention framework, a study website and delivery of information, has been established on the directional management level within all 13 districts within the Stockholm region and will be delivered directly to each intervention preschool after baseline measures and the randomization process. To increase parental engagement in the intervention group, participating parents will be provided with an information package (multi-lingual multi-media content) describing the intervention components, their importance, and practical information on how to engage in active transportation to/from preschool.

The intervention framework (on preschool level) includes:i.Formalized PA policies:A minimum of 3 h of total daily outdoor time, to be scheduled both in the morning and in the afternoon.At least 10 min of teacher-led active play per day. An activity bank will be provided for inspirations of possible teacher-led activities.A minimum of 1 weekly outdoor excursion which is commonly realized as a visit to local parks, playgrounds, or other recreational facilities. A map of recommendations of potential outdoor excursion areas will be provided.Meet the children outdoors when they arrive at preschool and/or picked up by their parents.Only use screen-based devices for educational teaching purposes.Communicating to, and encouraging, the parents to actively transport their children to and from the preschool.ii.A study website will provide information on the study process and measurements. The activity bank for inspiration of teacher-led active play and a map of recommendations for outdoor exertion, mentioned in PA policies b and c above, will also be accessible through the website. This study website may also serve as a platform for interprofessional education where preschool teachers can share and communicate about engagement in activities and their experience.iii.Weekly follow-up and feedback by web-based questionnaires to determine fidelity and dose of intervention.

As the intervention is an organizational change allocated to the cluster (preschool) level, there will be no modification of the intervention from the individual (participant) level. There are no special criteria for discontinuing the intervention. The participant who wishes to discontinue the intervention have been instructed to immediately notify the research group.

### Intervention development and theory base

The interest for the intervention began when the previously mentioned observational study found a positive association between having a formalized PA policy in preschools and children’s PA levels [27], which attracted attention from politicians and stakeholders in the City of Stockholm. Realizing the potential of policy to increase PA among preschool children, the stakeholders took a formal political decision that all public preschools in the Stockholm region should implement a formalized PA policy. This decision is documented in the public preschools’ financial steering plan and implies that all public preschools in the Stockholm region should exert effort and financial resources in the implementation of a PA policy. In addition, a policy package should be developed and evaluated to provide a “model” for preschools to understand what PA policies to implement and effective strategies for implementation. The intervention policy package has been developed in co-creation among the research group, municipal childcare stakeholders, district officers from the 13 Stockholm region districts and a reference group consisting of preschool principals and teachers. The policy package has been discussed and acknowledged among all co-creators to increase the engagement, buy-in, feasibility, relevance, and sustainability of the intervention policy package as recommended by a previous meta-analysis on the effectiveness in co-creation of research [36]. The Behaviour Change wheel [37] was chosen as a theory base to understand and reflect on essential conditions (capacity, opportunity, and motivation) for behavior change in relation to the intervention’s functions and policy category. (The detailed logical model of theory of change for the policy package intervention based on behavioral change wheel can be found in Additional file 4 theory of change).

### Implementation of the intervention

This intervention is expected to scale up upon proof of effectiveness and feasibility. Therefore, no special implementation facilitation will be provided—to ensure external validity. Specifically, to ensure complete scalability, we will utilize a pragmatic approach where minimal additional resources are provided (no support beyond that of the intervention package), thereby evaluating whether the routine resources disposable to Swedish preschools are sufficient for the implementation of the intervention. The implementation of the policy package will be examined in detail following the process evaluation framework by Moore et al. [38]. To which extent the policy package is implemented (dose and fidelity) is followed up weekly by web-based questionnaires. Implementing the intervention policy package will not require alteration to usual preschool care pathways. More details of process evaluation are illustrated in the “Outcomes and measures” section.

### Control condition

Preschools randomized to the control condition are not provided with the intervention package and are encouraged to keep their usual practice and routines during the intervention period. However, in this pragmatic trial, control preschools are also under the influence of financial steering document, and they are free to implement any PA policy. In addition, communication between teachers from intervention and control groups and the study website may contribute to contamination. Therefore, PA policies in control preschools will be monitored at baseline, mid-point (3 months), and endpoint (6 months) to capture possible contamination effects and understand the possible change in their PA policy throughout the intervention.

### Outcomes and measures

In the present study, several instruments are used to assess outcomes in children and teachers. An additional file provides an illustration of all the instruments used, corresponding to the measured outcome variable, time point of measurement, and group relevance (i.e., measurement in both intervention and control groups or intervention group only) in detail (See Additional file 5). Questionnaires will be distributed via email to each respondent through Webropool 3.0. All questionnaires used can be found in Supplementary material 3 questionnaires. Questionnaires answered by preschool personnel are distributed only in Swedish. The questionnaires distributed to parents are available in Swedish, English, Arabic, Turkish, Somali, Tigrinya, and Swahili to cater to the need of parents with language barriers as an effort to retain a study sample containing individuals from different countries of origins. The questionnaires included as additional files (see Additional files 6, 7 and 8) are only available in English and questionnaires in other languages can be made available upon reasonable request.

### Physical activity levels (primary outcome) and sedentary time (secondary outcome) in children

PA levels in children such as total PA, MVPA, light PA (LPA), ST, and steps will be measured objectively using triaxial GT3X+ accelerometers, which have been tested extensively for reliability and validity in both pediatric and adult populations [39]. Children will be instructed to wear the accelerometer, on the non-dominant wrist, for 24 h during 7 consecutive days except during water activities (e.g., when showering and swimming) at both baseline and 6 months follow-up. The non-dominant hand will be predetermined by parents (information collected together with informed consent). Setup and analysis of accelerometer data will follow validated age-specific criteria and recommendations [39]. The accelerometer data sampling frequency is 30 Hz and data will be analyzed at 1-s epochs which suits the sporadic movement pattern of preschool children [39]. Raw accelerometer data will be downloaded through Actilife and analyzed using the GGIR package [40]. The classification of PA intensities and ST will follow the cut-offs developed for children with wrist-worn Actigraph GT3X+ by Hildebrand et al. [41, 42]. Steps will be determined using the Verisense step algorithm, which is integrated in GGIR to determine steps for wrist-worn accelerometry [43]. Accelerometer data consisting of ≥ 10 h/day wear time with > 3 days of measurement days will be considered valid [44]. However, participants with less valid days will be included in sensitivity analysis.

Results will be reported in categories of PA during the preschool time, PA outside preschool time, and PA during the entire day. This is to explore how the preschool policy affects PA during the preschool time frame and to assess potential extended effect beyond the preschool time frame and compensatory behavior [45]. Change in MVPA will be emphasized since PA in higher intensity is suggested to have greater benefits for health outcomes [3].

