### Sleep of children (secondary outcome)

Sleep will be measured using a combination of 24 h accelerometry, a sleep time diary during periods of accelerometer measurements, and a parental questionnaire to reflect sleep quality during the past 6 months. All measurements for sleep will be conducted at baseline and 6 months follow-up. Sleep onset, sleep duration, and waking up will be determined by algorithms integrated in GGIR [48]. Appropriate algorithms for detection of sleep in children will be used. The sleep time diary included in the parental measurement week questionnaire consists of two questions regarding children’s wake up time and bedtime. In addition, parents will answer questions in SDQ and sleep questionnaire about children’s sleep duration and quality during the past 6 months and these questions are adapted from the validated Ages and Stages Questionnaire [49]. To minimize the burden of answering different questionnaires, the sleep quality questions were added to the SDQ questionnaire; therefore, the questionnaire is named SDQ and sleep questionnaire.

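### The accelerometer validity rule counts any 10 h of a 24-h recording and sets no minimum for each reporting window, so days with little waking or preschool-time data can pass

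*Protocol article*

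**What the plan says.** All of the following comes from the protocol article.

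- **Wear protocol** (section on physical activity levels and sedentary time in children): the device is worn "for 24 h during 7 consecutive days except during water activities", at baseline and at 6 months.
- **Validity rule** (same section): "Accelerometer data consisting of ≥ 10 h/day wear time with > 3 days of measurement days will be considered valid".
- **Reporting windows** (same section): "Results will be reported in categories of PA during the preschool time, PA outside preschool time, and PA during the entire day".
- **Children below the day threshold** (same section): "However, participants with less valid days will be included in sensitivity analysis".
- **General processing statement** (same section): "Setup and analysis of accelerometer data will follow validated age-specific criteria and recommendations".
- **Sleep** (section on sleep of children): "Sleep will be measured using a combination of 24 h accelerometry, a sleep time diary during periods of accelerometer measurements". Sleep onset, duration and waking are to be derived with the algorithms in GGIR.
- **Allowance for poor wear** (section on study population and recruitment): "we expect an estimated accelerometer non-compliance rate of 10% (i.e., participants with insufficient wear time) and a dropout rate of 20" per cent.

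The rule does not mention waking time, type of day, or wear within preschool hours.

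**The concern.** A threshold of 10 h per day screens out poor data when the device comes off at night. With a 24-h protocol, sleep alone may reach it. The policy works largely through the preschool day, for example "A minimum of 3 h of total daily outdoor time, to be scheduled both in the morning and in the afternoon", so the hours that matter most are those the rule does not require.

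Two things are at stake. First, a day may enter the primary outcome with almost no time in which moderate-to-vigorous activity (MVPA) could occur, or with no observation of the preschool window. Second, the entire-day average mixes weekdays and weekend days in proportions that vary by child and by visit. The primary outcome is a change from baseline, so a different mix at the two visits enters the change score directly. The one sensitivity analysis stated on wear adds children with fewer valid days, so it cannot show either problem.

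**Working it through.** The article gives no figure to reproduce here, so the check asks what the rule accepts.

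**Inputs from the article:** at least 10 h per day; more than 3 days, hence at least 4, of 7 consecutive days (5 weekdays and 2 weekend days); planning effect 5 min MVPA and SD 25 min (sample size section).

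**Assumptions, not in the article:** preschool day 6 to 12 h; night sleep 8 to 12 h; in step 4, a policy effect of d minutes on weekdays only; in step 5, a weekday-weekend gap in MVPA of 20 min, with half and one and a half times that as the range.

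1. **Night wear.** Wear from 20:00 to 24:00 and from 00:00 to 07:00 gives 4 + 7 = 11 h in a calendar day. This is at least 10 h, so the day is valid.

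2. **Hours needed elsewhere.** Time outside preschool is 24 − 6 = 18 h down to 24 − 12 = 12 h, always above 10 h. A weekday can therefore pass with no preschool-time wear. Waking wear needed is max(0, 10 − sleep): 2 h with 8 h of sleep, 1 h with 9 h, and 0 h with 10 h or more.

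3. **Which days.** There are 35 ways to choose 4 days of 7: 10 contain two weekdays, 20 contain three and 5 contain four. At least 2 weekdays are always present. Over all accepted patterns of 4 to 7 days, the weekday share runs from 2/4 = 0.50 to 4/4 or 5/5 = 1.00. A full week gives 5/7 = 0.714.

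4. **Expected effect on the entire-day mean.** A child with weekday share w shows w × d. With d = 7 min this is 3.5 min at w = 0.50, 5.0 min at 5/7 and 7.0 min at 1.00. Averaged over the 35 equally likely four-day sets, the share is (10×2 + 20×3 + 5×4)/(35×4) = 100/140 = 5/7. Random loss of days therefore leaves the expected effect at 5.0 min.

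5. **Noise.** If every child had exactly 4 random days, the variance of the number of weekdays would be 4 × (5/7) × (2/7) × (3/6) = 0.408. The variance of the share is 0.408/16 = 0.0255, so its SD is 0.16. With a 20-min gap this adds an SD of 0.16 × 20 = 3.2 min, a variance of about 10 min². Against 25² = 625 min² that is 1.6% per time point. A 10-min gap gives 0.0255 × 100 = 2.6 min², or 0.4%. A 30-min gap gives 0.0255 × 900 = 23 min², or 3.7%. Children with more than 4 valid days contribute less.

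6. **Number affected.** The article gives no distribution of wear by hour or day, so this cannot be computed.

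**The case against.** The strongest reply is that this is a condensed article. The rule carries a citation, and the processing statement points to age-specific recommendations. Either source, or a full analysis plan, may limit wear to waking hours or set rules by window. That is possible and lowers confidence. But the article does more than stay silent: it prints a numerical rule beside a 24-h wear protocol and three reporting windows, and the rule as printed fits neither. Night-only wear is also a constructed extreme, since children are told to wear the device all day. That stands too.

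A reader might infer more than the article supports:

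- **Weekend wear alone satisfies the rule.** It does not; at least 2 of any 4 valid days are weekdays.
- **The preschool-time estimate is diluted by weekend days.** Weekend days contain no preschool time. The article does not say that a child without preschool-time wear is scored as zero.
- **The trial would report between 3.5 and 7 min for a true 5.** Those are single-child extremes. The trial estimate would read 3.5 only if every child had two weekdays and two weekend days.
- **The estimate is pulled towards zero, or biased between arms.** Day mix can push it either way. The article hypothesises less illness absence under the policy, so a difference in attendance between arms is conceivable, but nothing shows that wear or day mix would differ.

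The assumption that the effect falls on weekdays only is also open to question, because the article plans to look for effects beyond preschool time.

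**Conclusion.** The point holds in a limited form. The printed rule lets a day of mostly evening and night wear count as valid and does not ensure that the preschool window is observed. It also leaves the entire-day mean dependent on a weekday share between 0.50 and 1.00 that may change between visits. The cost is mainly precision: about 0.4% to 3.7% of the planning variance per time point from day mix, if every child had only 4 randomly lost days and the weekday-weekend gap were 10 to 30 min. Noise from days with little waking wear comes on top and cannot be sized from the article. The hours argument holds over the whole assumed range of preschool-day length; night wear supplies the full 10 h only if sleep is 10 h or longer. Systematic bias is not shown. This is a cheap improvement, not a threat to the trial's conclusions.

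**What to change.** Amend the rule before the analysts learn the allocation:

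- Count the 10 h in waking hours, using the GGIR sleep detection and the wake-up and bedtime diary already planned.
- Compute preschool-time activity only from days on which a stated minimum share of preschool hours was worn, and treat it as missing otherwise. The article supports no particular share, so the sponsor should choose and state one.
- Where both day types are available, compute entire-day activity as (5 × weekday mean + 2 × weekend mean)/7 at both time points. Say in advance what is done when only one type is available.
- Keep the present rule as a sensitivity analysis.

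Do not make validity depend on a minimum number of attended days. Attendance is observed after randomisation, and illness absence is itself a secondary outcome that the policy is expected to reduce, so such a condition could introduce selection.

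The cost is wording and a change to the processing script, with no new data. Slightly fewer child-days will be valid in the main analysis, so the 10% allowance for insufficient wear should be checked against the amended rule.
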